## Abstract

**Aims:**

Recurrent congestive episodes are a primary cause of hospitalizations in patients with heart failure. Hitherto, outpatient management adopts a reactive approach, assessing patients clinically through frequent follow-up visits to detect congestion early. This study aims to assess the capabilities of a self-supervised contrastive learning-derived risk index to detect episodes of acute decompensated heart failure (ADHF) in patients using continuously recorded wearable time-series data.

**Methods and results:**

This is the protocol for a single-arm, prospective cohort pilot study that will include 290 patients with ADHF. Acute decompensated heart failure is diagnosed by clinical signs and symptoms, as well as additional diagnostics (e.g. NT-proBNP). Patients will receive standard-of-care treatment, supplemented by continuous wearable-based monitoring of vital signs and physical activity, and are followed for 90 days. During follow-up, study visits will be conducted and presentations without clinical ADHF will be referred to as ‘regular’ and data from these episodes will be presented to a deep neural network that is trained by a self-supervised contrastive learning objective to extract features from the time-series that are typical in regular periods. The model is used to calculate a risk index measuring the dissimilarity of observed features from those of regular periods. The primary outcome of this study will be the risk index’s accuracy in detecting episodes with ADHF. As secondary outcome data integrity and the score in the validated questionnaire System Usability Scale will be evaluated.

**Conclusion:**

Demonstrating reliable congestion detection through continuous monitoring with a wearable and self-supervised contrastive learning could assist in pre-emptive heart failure management in clinical care.

**Clinical trial registration:**

The study was registered in the German clinical trials register (DRKS00034502).

## Introduction

Heart failure (HF) is the most common cause of hospitalization and in-hospital death in Germany.^1^ After discharge, 17% of patients with HF are rehospitalized for HF within 90 days.^2^ Recurrent hospitalizations of respective patients due to HF increase the risk of adverse events, and these are associated with high mortality rates of almost 12%.^3,4^ Up to 70% of HF-related hospitalizations are driven by acute decompensated HF (ADHF).^5^ Acute decompensated HF can be triggered by various mechanisms such as hypertensive episodes or arrhythmias.^6,7^ Hitherto, outpatient management of HF patients relies on self-assessment of symptoms and tracking of single parameters like body weight. This approach places a significant burden on patients, requiring them to handle standardized parameters and possess a certain level of health literacy.^8^ To reduce the risk of hospitalizations, patients with HF are frequently re-examined and clinically assessed according to fixed schedules to detect decompensation early.^9^ These visits involve clinical assessment with specialized personnel, laboratory measurements, and adjunctive diagnostic modalities, which are resource-intensive and pose a significant burden to specialized outpatient clinics.^10^ Hence, there is a need for innovative and individualized concepts for pre-emptive detection of congestion in patients with HF that reduce the burden on the healthcare system.

Implementation of digital tools for assessing early clinical signs of congestion represents an option for the management of patients with HF and potentially facilitates early treatment interventions.^11^ Cardiac implantable electronic devices and implantable pulmonary artery pressure sensors are promising methods for detecting congestion early; however, they require an invasive implantation procedure.^11,12^ Devices measuring bioelectrical impedance show comparable results in detecting congestion; however, they require active patient engagement.^13^

Small, portable devices known as ‘wearables’ offer a novel option for non-invasive monitoring of vital parameters and physical activity.^14^ These devices utilize established sensor technologies such as photoplethysmography, accelerometry, and temperature probes to continuously record data about relevant parameters for medical monitoring. However, despite their potential, wearables are predominantly used for sports and lifestyle monitoring, with medical applications remaining relatively scarce. This scarcity is primarily due to the challenge of extracting clinically actionable information, or digital biomarkers, from the extensive data generated by wearables. A study with multi-parameter adhesive chest wearables and advanced analytics showed good accuracy in detecting impending hospitalizations but revealed adherence issues that may hinder the widespread clinical application of wearables.^15^ There is a need for unobtrusive systems that enable longitudinal and passive monitoring of patients with HF.

In a previous study, we demonstrated the feasibility of detecting clinical complications such as infections and arrhythmias leveraging wearable data obtained in oncology patients undergoing chemotherapy by computing a risk index using deep learning analysis (‘self-supervised contrastive learning’).^16^

In this study, the aim is to evaluate the accuracy of a similar risk index in detecting ADHF in patients with HF, assess the data integrity, and explore the patients’ perspective.

## Methods

### Study design and setting

This is an investigator-initiated, single-centre, single-arm, prospective cohort pilot study including patients with ADHF. The study will be conducted at the Department of Cardiology, Angiology, and Intensive Care Medicine of the University Hospital RWTH Aachen. The study was approved by the ethics committee of the Medical Faculty of University Hospital RWTH Aachen and was registered in the German clinical trials register (DRKS00034502). This study will be conducted according to the Helsinki Declaration.

Patients will be informed that they will not derive immediate individual benefits from study participation. All patients will sign a written informed consent before study inclusion. Recruitment will start in December 2024, and study duration is planned for 24 months. There will be no study-related follow-up of the patients after completion of the study.

### Participants

Inclusion criteria will be patients’ age ≥ 18 years with ADHF confirmed within the last 24 h. Acute decompensated HF is defined as worsening in dyspnoea at rest or with minimal activity, one or more accompanying signs (jugular venous pulsation ≥ 11 cm, hepatomegaly, peripheral oedema), and one or more objective measures of heart failure (six minute walking test < 200 m, N-terminal proBNP level ≥ 1000 pg/mL or a two-fold increase to baseline).^17^ Additionally, one of the following findings has to apply: chest X-ray (presence of pulmonary venous congestion or small pleural effusion) or vena cava imaging (one of two max. diameter > 2.2 cm and/or collapsibility < 50%) or lung ultrasound (more than three B-lines in more than two intercostal spaces bilaterally are considered diagnostic for the detection of interstitial and alveolar oedema). Exclusion criteria are defined as active malignant disease, pregnancy, active severe systemic infection (requiring intravenous antibiotic treatment), end-stage renal disease with dialysis, medical or mental conditions impairing the ability to continuously wear the wearable (e.g. dementia, skin abnormalities), and active implants, which might impair recordings (detailed inclusion and exclusion criteria are listed in *Table 1*).

**Table 1 ztaf004-T1:** Inclusion and exclusion criteria for the CONAN study

Inclusion criteria	Exclusion criteria
Clinically confirmed congestion within the last 24 h NYHA ≥ II Age ≥ 18 years and able to understand the design and objectives of the study Signed written informed consent and data safety agreement before any study-related activities Willingness to wear the wearable during the treatment period and return it on a follow-up visit	Active malignant disease Pregnancy Active severe systemic infection, defined as intravenous administration of antibiotics End-stage renal disease with dialysis Medical or mental conditions, such as dementia, that hinder the continuous use of the monitoring platform and associated equipment during the monitoring period Any condition that makes wearing the wearable device impossible (e.g. presence of a shunt, active bleeding, or absence of limbs) Mental incapacity or language barriers that preclude adequate understanding or cooperation, known or suspected not to comply with study directives or not to be reliable or trustworthy, or a subject who in the opinion of the investigator should not participate in the study

### Study procedures

In- and outpatients with ADHF will consecutively be screened for in- and exclusion criteria at the cardiology department at University Hospital RWTH Aachen (*Figure 1*). All patients will be treated according to the standard of care, and the study visits will be scheduled accordingly. The monitoring period starts from the inclusion of the patients into the study followed by continuous monitoring of vital signs and physical activity by the wearable for 90 days. Based on the decision by the treating physician eligible patients will be admitted for treatment to the study site or will be treated as outpatients. Follow-up visits are conducted on the day of discharge and in accordance with the guideline-based follow-up recommendations for patients experiencing ADHF, routine outpatient visits at the HF clinic will be scheduled ∼14 and 90 days post-discharge. If the patient initially receives inpatient treatment, the day of discharge and any unplanned visit to the outpatient clinic of the study site will be documented as study visits.

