**Figure 1 ztaf004-F1:**
[figure not shown]
During the CONAN study, clinical congestion assessment will be conducted at study visits. These procedures will be consistently repeated at each visit. Subsequently, clinical endpoints will be evaluated.

The baseline visit of a given patient will be conducted within the initial 24 h after diagnosis of ADHF. During the baseline visit, the following data will be obtained: medical history including HF entity, comorbidities, symptoms, signs, vital signs, laboratory values, and bioelectrical impedance analysis (*Table 2*). Bioelectrical impedance analysis will be performed by clinical staff to assess the patient’s total body water composition. Additionally, the EVEREST Score will be computed that serves as an established clinical tool for assessing congestion in patients with HF. The score scales rate congestion severity, utilizing clinical parameters such as dyspnoea, orthopnoea, oedema, and jugular venous pressure.^18^ Three paper-based validated questionnaires will be used to assess digital health literacy (HLS_19_-DIGI) overall, self-care behaviour in HF using the nine-item European Heart Failure Self-care Behaviour Scale (EHFScB-9), and the Kansas City Cardiomyopathy Questionnaire (KCCQ-12), which assesses the quality of life in patients with HF.

**Table 2 ztaf004-T2:** Study procedures during the CONAN study

Procedures	Baseline (V_Baseline_) Confirmed ADHF Day 0/+24 h	Visit a (V_a_) In the case of inpatient treatment, the day of discharge	Visit 1 (V_1_) Regular outpatient visit Day +14 days (±7 days)	Visit *n* (V*_n_*) Any unplanned clinic visit (i.e. ER visit) Day +*n*	Visit end-of-study (V_EOS_) Regular outpatient visit Day +90 days ± 14 days
Inclusion/exclusion criteria	X				
Demographics	X				
Past medical history incl. HF entity	X				
Concomitant medication	X	X	X	X	
Vital signs and body weight	X	X	X	X	X
HLS_19_-DIGI	X				
Kansas City Cardiomyopathy Questionnaire (KCCQ-12)	X				X
European Heart Failure Self-care Behaviour Scale (EHFScB-9)	X				X
Safety/Deficiencies Assessment		X	X	X	
EVEREST Score^18^	X	X	X	X	X
Mobile Application Rating Scale (MARS-G)^19^					X
System Usability Scale (SUS)					X
Bioelectrical impedance	X	X	X	X	X
Parameters using the *monti* platform					
Connection attempts to the server		X	X	X	X
Number of daily ECG recordings		X		X	X
Completed uploads including timestamp and file size		X	X	X	X
Failed uploads		X	X		X

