Completeness of vital signs and physical activity time-series data:		X	X		X
Number of notifications and type (e.g. reactivate/charging)		X	X		X
Number and type of contacts (e.g. phone call for technical support)					X

During follow-up visits, symptoms, signs, and vital signs will be assessed. As part of the safety assessments, local skin reactions or discomfort are monitored, and the technical equipment is inspected for any obvious damage. Moreover, details regarding HF hospitalizations and all unplanned, non-trauma-related hospitalizations and emergency department visits will be recorded. During the visit at 14 days post-discharge, the first 10 patients will complete the System Usability Scale (SUS) to identify any potential deficits in the monitoring platform that can be iteratively optimized. The SUS measures the overall usability of a system by capturing user perceptions of its ease of use and learnability. As there are multiple translations to German, the version of Rummel *et al*. was chosen.^20^

The end-of-study visit will be scheduled on Day 90 post-initial discharge, with a window of plus or minus 14 days. EHFScB-9 and KCCQ-12 questionnaires are completed by the patients again. Additionally, the SUS and Mobile App Rating Scale (MARS-G) questionnaires will be handed out to the patients. These are validated tools used to assess the quality and usability of digital health applications.^19^ MARS-G evaluates various aspects of mobile app performance, including engagement, functionality, aesthetics, and information quality. In the event of withdrawal of consent, patients will be asked to complete an end-of-study visit at the earliest possible date.

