All study equipment will be collected at the end-of-study visit. In the event that no data is received from an enrolled patient for 1 day, the patient is reminded via a push notification to use the monitoring system. If no data is received for 2 consecutive days, the patient is contacted by phone to determine whether there is a technical problem. If the patient wishes to terminate the study, he will be excluded and asked to return the devices at the next regular visit to the study site. If this is not possible, the study team can offer to collect the devices at the patient’s home. If a patient is lost to follow-up, he will be contacted during the next regular visit to the study site to return the equipment.

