### Data collection

Wearable data and ePRO data will be transmitted by monti via mobile data services to a centralized server that runs real-time data analysis and analysis software. The data recorded by the wearable will include time-series data of raw signals as well as vital signs and physical activity parameters, with the latter computed using proprietary algorithms provided by the manufacturer. Vital signs and physical activity parameters, such as heart rate, temperature, respiratory rate, and physical activity, will be recorded at a rate of up to 1 Hz. Thus, up to 3600 data points are potentially generated per hour, each paired by a corresponding quality index. On the platform backend, data integrity is assessed by monitoring actual wearing time, both initial and ongoing app usage, and overall data quality. Data integrity assessments are conducted at interim study visits and the study’s conclusion (*Table 2*).

Clinical records (visit entries, laboratory results, diagnostic results) will be documented in worksheets. Records will be independently and retrospectively reviewed by two cardiologists for the presence of ADHF. Worksheet entries and results of the validated questionnaires are transferred into a database.

Time-series data recorded by the wearable will be annotated based on clinical records. At each follow-up visit, where a clinical congestion assessment is conducted, the 2 days prior and post-visit are annotated as either ADHF or regular, as determined by the congestion assessment on the visit day.

Exploratively, the dataset of regular episodes may be enriched by including episodes beyond this initial 2-day window if patients report stable symptoms and vital signs through the app. This approach allows for the evaluation of whether these additional episodes show consistent ‘regular’ patterns suitable for model training. Datasets will be split into hours according to their timestamps, and only hours with a >90% amount of data points will be included to ensure sufficient information content among hours. No predefined quality constraints are used.

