### Outcome and objectives

The primary outcome of this pilot study with the monti platform will be the accuracy of detecting episodes with diagnosed ADHF by a self-supervised contrastive learning-derived risk index based on wearable-recorded time series assessed through *C*-statistics (*Table 4*). As a secondary outcome data integrity will be assessed through the percentage of wearable data per day, the time difference between logged time point of measurement and database, and the score in the SUS, will be evaluated. Additionally, several exploratory endpoints will be examined.

**Table 4 ztaf004-T4:** Objectives and outcome measures of the CONAN study

	Outcome measures
Primary objective	
Assess the capability of the self-supervised contrastive learning-derived risk index (from wearable-recorded time series) to detect episodes of acute decompensated heart failure (ADHF).	Area under the receiver operating characteristics (AUROC) curve for detecting episodes of diagnosed ADHF.
Secondary objective	
(2) Evaluate the data integrity of the *monti*-monitoring platform in terms of adherence, technical functionality, and data quality.	Adherence: Daily percentage of wearable data availability. Percentage of data availability over participation period. Availability of each parameter per day. Number of app-server connection attempts. Number of uploaded vital signs. Number of recorded ECGs. Number of dropouts. Technical functionality: Ratio of failed uploads to total uploads. Number/type of notifications sent via the app. Number/type of user contacts. Mean time difference between measurement and database logging. Data quality: Mean percentage of data with high quality indices determined by the wearable for each parameter per day.
(3) To assess usability of the mobile *monti* platform	Mean score on the System Usability Scale (SUS). Percentage of users rating the app as ‘easy to use.’
(4) Monitor adverse events, including device-related effects and deficiencies.	Number of skin reactions or discomfort. Number of observed device damages.
Explorative objective	
(5) Expansion of the dataset by including additional ‘regular’ episodes	Number of ‘regular’ episodes included for training, annotated based on the 2-day window of study visits. Number of the additional ‘regular’ episodes included for training, annotated based on patient-reported stable symptoms and vital signs via the app. AUROC detecting episodes with diagnosed ADHF with expanded training data.

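### Wearable monitoring is timed from inclusion but the end-of-study visit from discharge; the device is handed in at that visit, and Table 2 schedules no safety assessment there

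*Protocol article*

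**What the plan says.** Five statements in the protocol article bear on the end of follow-up.

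- **Monitoring clock (Study procedures).** The starting point is inclusion, not discharge: "The monitoring period starts from the inclusion of the patients into the study". The same sentence then fixes the length of the period: "followed by continuous monitoring of vital signs and physical activity by the wearable for 90 days".
- **Visit clock in the text (Study procedures, after Table 2).** "The end-of-study visit will be scheduled on Day 90 post-initial discharge, with a window of plus or minus 14 days".
- **Visit clock in Table 2.** The column for this visit reads "Regular outpatient visit Day +90 days ± 14 days", in a table whose baseline column is day 0. Discharge is not mentioned in that column.
- **Device return (Wearable-based monitoring platform).** "All study equipment will be collected at the end-of-study visit".
- **Annotation rule (Data collection).** At each follow-up visit with a congestion assessment, "the 2 days prior and post-visit are annotated as either ADHF or regular".

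On safety, the Table 2 row "Safety/Deficiencies Assessment" is ticked at the discharge visit, the 14-day visit and unplanned visits. It is blank at end of study. The text after Table 2 describes skin checks and equipment inspection as part of follow-up visits without excepting any visit. Secondary objective 4 in Table 4 has "Number of skin reactions or discomfort" and the count of damaged devices as its outcome measures.

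**The concern.** The monitoring period and the end-of-study visit run on different clocks. For a patient treated as an inpatient, 90 days from inclusion is over before 90 days from discharge. A study team that follows the monitoring sentence to the letter could stop recording before the visit whose surrounding days are to be labelled, and such data cannot be recovered later.

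The Discussion calls a robust set of regular episodes a prerequisite for good detection and relies on the 2-day window to supply it. Scheduled follow-up visits are few: three for inpatients (discharge, 14 days, end of study) and two for outpatients. The end-of-study visit is the one furthest from the index decompensation.

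The blank safety cell concerns a different outcome. If the table is followed, nothing prompts a record of skin reactions or damage when the device is handed back, after the longest stretch of wear.

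**Working it through.** The plan gives no figure of its own on this point, so there is none to reproduce. No input to the sample size depends on visit timing.

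**Inputs.** Monitoring: days 0 to 90 from inclusion. End-of-study visit: day 90 after discharge with offset o from −14 to +14. Annotation window: 2 days before and 2 days after, 4 in all. Length of stay L: not stated, so I assume 0 to 14 days. An outpatient has no discharge date; I set L = 0 with inclusion as day 0.

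**Step 1: visit day from inclusion.** t = L + 90 + o.
- L = 0: day 76 to 104
- L = 7: day 83 to 111
- L = 14: day 90 to 118

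Table 2, counted from baseline, gives day 76 to 104 for everyone. Text and table therefore agree only for L = 0.

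**Step 2: days after the visit.** The device is collected at the visit, so 0 of these 2 days can be recorded for any patient, whatever L and o. The maximum is 2/4 = 50% of the window.

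**Step 3: days before the visit if recording stops on day 90.** Days with data = 92 − t, limited to between 0 and 2.
- t ≤ 90: 2 of 4 days (50%)
- t = 91: 1 of 4 days (25%)
- t ≥ 92: 0 of 4 days

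For an on-time visit (o = 0) this gives 50% at L = 0, 25% at L = 1 and 0% at L ≥ 2.

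If the 29 whole-day offsets from −14 to +14 are taken as equally likely (an assumption), the share of visit days with an empty window is:

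| Assumed L | Offsets with t ≥ 92 | Share |
|---|---|---|
| 0 | 13/29 | 45% |
| 2 | 15/29 | 52% |
| 7 | 20/29 | 69% |
| 14 | 27/29 | 93% |

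**Step 4: days before the visit if the device is worn until it is handed in.** 2 of 4 days (50%) for every patient, whatever L and o.

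**Step 5: safety schedule.** The last scheduled tick is at the 14-day visit. From there to the end-of-study visit is nominally 90 − 14 = 76 days, on either anchor. With the Table 2 windows (±7 and ±14 days) the gap runs from 76 − 21 = 55 to 104 − 7 = 97 days. On the table alone, only an unplanned visit would bring a safety record in that time.

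**The case against.** The strongest reply is that nothing orders recording to stop on day 90. The patient keeps the equipment until the end-of-study visit, and a day without data triggers a reminder. Data collection is said to run until withdrawal. Table 2 gathers connection attempts, uploads and time-series completeness at end of study. The 90 days may simply be the nominal length. This stands: the empty window follows only from the literal reading.

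Nor does the annotation rule need a complete 4-day window. Data are cut into hours, and hours with more than 90% of their data points are kept. Missing post-visit hours drop out, so a special pre-visit-only rule for this visit would change nothing. This stands too.

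Several stronger conclusions are tempting but not supported:

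- **That decompensation found at the end-of-study visit is unusable.** If the device is worn to the visit, up to 48 labelled hours before it remain, as does the 7-day look-back planned under Statistical analysis. Only the look-forward after diagnosis is lost.
- **That a third of inpatients' scheduled windows are lost.** This needs both the literal day-90 stop and an assumed stay, and it ignores visits held early in the ±14 days.
- **That 76/90 = 84% of follow-up lacks a scheduled safety check.** This puts the 14-day visit at day 14 from inclusion. With the discharge anchor and an assumed stay of 5 to 10 days, that visit falls on day 19 to 24, leaving 71 to 66 of 90 days, or 79% to 73%.
- **That device effects after the 14-day visit go unrecorded.** The text describes safety checks for follow-up visits generally, and Study procedures counts the 90-day visit among them. What exists is a conflict between table and text.

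**Conclusion.** The point holds as a conflict in the schedule. Monitoring, the end-of-study visit in the text and the same visit in Table 2 use anchors that disagree for any inpatient.

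It is certain that the 2 post-visit days at end of study cannot be recorded, so this visit supplies at most half of the stated window. It is conditional that the window is empty: that needs a literal stop on day 90 and, for an on-time visit, a stay of at least 2 days. If the device is worn until returned, the 2 pre-visit days are kept for everyone.

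The safety row of Table 2 conflicts with the text. Followed as it stands, it would undercount the outcomes of secondary objective 4 that arise after the 14-day visit.

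The sample size and the definition of the primary outcome are unaffected. The change is still worth making, because recording that has stopped too early cannot be made good afterwards and the repair is cheap.

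**What to change.** 1. State in Study procedures that wearable recording continues until the end-of-study visit, whenever it falls within its window.
2. Use one anchor, inclusion or discharge, for monitoring and visits in both the text and Table 2. If discharge is chosen, say what day 0 is for outpatients.
3. Add the safety and deficiencies assessment at the end-of-study visit in Table 2, in line with the text on follow-up visits.

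The cost is protocol wording and one table cell, with no extra visit. Some patients wear the device longer than 90 days. For an on-time visit the extra time equals the length of stay, and a late visit adds at most 14 days. The post-visit half of the window stays empty after this change.
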